### **5.2 Statistical methods for secondary outcomes**

For the secondary outcomes, similar repeated measures LMMs will be applied as the primary outcomes. Each secondary outcome measure will serve as the dependent variable. Covariates will include age, biological sex, and motion parameters if they are found to associate with outcomes. For our secondary analysis, well-established multiple comparison adjustment methods will be applied. For neuroimaging data, cluster-based correction methods will be used to control the family-wise error rate (FWER). For non-neuroimaging data, False Discovery Rate (FDR) adjustments will be applied to control for false positives. Additionally, we propose an exploratory option of using principal component analysis (PCA) to form components from correlated measures to reduce dimensions of our data.

Correlation analysis and cutting-edge mediation analysis will be used to understand the relation between MDMA induced brain changes and MDMA induced changes in behavioral and experiential measures.

### **5.3 Interim analyses**

We plan the power of our study to be able to detect a small effect of MDMA on brain activation. However, recent studies have shown that this effect can be in the medium range in tasks similar to the ones we have adopted. Therefore, we will run interim analyses to determine if our effects of interest can already be detected when we collect N = 17 participants.

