## **2.5 Interventions**

### *2.5.1 Intervention description*

After baseline visit, each participant will receive placebo, 80mg MDMA HCl, and 120mg MDMA HCl in a randomized order. Given the within-subjects design of the study, each participant will receive all three of the specified doses across the duration of the trial. Drug visits will be scheduled 10-14 days apart to avoid drug carry-over effects. Participants will arrive fasted for drug visits in the morning to reduce the risk of emesis. They will complete a urine drug screen and pregnancy test (if applicable) and have their baseline vitals recorded at the Stanford Center for Cognitive and Neurobiological Imaging, where they will be met by the study clinician. Participants will be instructed to orally ingest pills with water or an electrolyte solution. For safety reasons, pulse, blood pressure, temperature, and oxygen saturation will be monitored and recorded every 30 minutes throughout the drug visit. The total visit time for drug visits will be 6-8 hours.

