### *2.6.2 Concealment mechanism*

With our analysis plan and recruitment goal informing the number of randomization assignments, we will use randomization.com to create a random order dose assignment (80mg, 120mg, and placebo) for each of the 40 study IDs. Study IDs are sequential, starting with 001 and ending with 040.

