## **2.10 Recruitment and Study Cohort**

Healthy volunteers who report  $\geq 2$  uses of MDMA when they were 18 years or older, recruited to attain 4 sessions of data during functional brain imaging. A total of 40 participants will be recruited, equal

numbers of males and females will be recruited. Participants will be recruited through Facebook Ads using IRB-approved material. Individuals who express interest in the study will be directed to an online screening survey in REDCap. Completed screening surveys will be reviewed by research coordinators trained on the study protocol. Surveys will collect information about demographics, psychiatric diagnoses, substance use, and MRI compatibility. Individuals that are eligible by the criteria included in the screening survey will be contacted by a research coordinator to schedule a phone call. On this phone call, research coordinators will give the individuals additional information about the study and collect additional demographic information. Eligible individuals at this point will be consented by a research coordinator and will schedule an in-person screening visit at a research clinic to fully determine eligibility. The following procedures and assessments will be performed at the screening visit: ECG, physical examination, blood draw, vital signs, weight, urine drug test, pregnancy test (if applicable), Hamilton Anxiety Rating Scale (HAM-A), Hamilton Depression Rating Scale (HAM-D), the Mini International Neuropsychiatric Interview (MINI).

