## **5. Statistical methods**

### **5.1 Statistical methods for primary outcomes**

To assess MDMA-induced acute changes in the regional circuit scores derived from the conscious and nonconscious FEET task, repeated measures linear mixed-effects models (LMMs) will be applied. Each outcome measure will serve as the dependent variable, with Dose (placebo, 80mg MDMA and 120mg MDMA) as a within-subjects fixed effect. Further, to assess whether baseline neural profile could predict distinct MDMA-induced acute changes, a median split approach to stratify participants into the high and low activity or connectivity groups and examine the modulation effect of the group. A separate LMM with Dose and Subgroup and their interaction as fixed effects will be implemented. We will focus on the between-subgroup difference between placebo and 120mg MDMA, as well as between placebo and 80mg MDMA. The inclusion of the 80mg dose enhances understanding of dose-dependent MDMA-induced effects and improves blinding. Covariates will include age, biological sex, and motion parameters if they are found to associate with outcomes. For our primary analysis on the pre-registered circuit measures, we will not perform multiple comparison correction as they measure overlapping constructs and do not meet strict criteria for independent measures. We acknowledge the issue of multiple measures, as the detailed set of assessments may measure overlapping constructs and may not meet strict criteria for independence. An alternative approach involves identifying measures that show significant MDMA-induced effects using a  $p < 0.05$  threshold, examining the correlations among these effects, and selecting the measures with the greatest MDMA-induced effect sizes. Additionally, we propose an exploratory option of using principal component analysis (PCA) to form components from correlated measures to reduce dimensions of our data.

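### Section 5.3 says the study is powered for a small MDMA effect, but under conventional readings 40 participants give 80% power only for a paired difference of about 0.45 SD

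*Protocol*

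**What the plan says.** The protocol's only statement about power is in section 5.3 (Interim analyses): "We plan the power of our study to be able to detect a small effect of MDMA on brain activation". The next sentence sets this against a larger possibility, that "recent studies have shown that this effect can be in the medium range in tasks similar to the ones we have adopted", and on that ground introduces an interim look at N = 17.

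The sample size is fixed elsewhere. Section 2.10 says "A total of 40 participants will be recruited", and section 2.6.2 generates a dose order "for each of the 40 study IDs". Under section 2.5.1, "each participant will receive all three of the specified doses across the duration of the trial". The primary model in section 5.1 is a linear mixed model "with Dose (placebo, 80mg MDMA and 120mg MDMA) as a within-subjects fixed effect", and for the primary circuit measures "we will not perform multiple comparison correction".

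The protocol gives no numerical effect size, power, SD, within-person correlation or calculation that connects 40 participants to a small effect.

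**The concern.** Section 5.3 presents sensitivity to a small effect as a property of the design. Every participant receives every dose, so a placebo-versus-dose contrast in the section 5.1 model is in effect a paired comparison on at most 40 people. On the usual scale, where small is about 0.2 and medium about 0.5, 40 pairs are enough for something close to a medium effect but not for a small one.

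This is the only power statement in the protocol, so it is what a reader would use to interpret a non-significant circuit result. If it is wrong, such a result carries much less information about small effects than the text implies. The interim look is also motivated by the same contrast between small and medium.

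**Working it through.** **Inputs from the protocol**
- N = 40 (sections 2.6.2 and 2.10), all three doses within person (section 2.5.1).
- Threshold 0.05 (section 5.1), with no multiplicity correction on primary measures.
- Interim look at N = 17 (section 5.3).

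**Assumptions, because the protocol gives no figure**
- Small = 0.2 and medium = 0.5 as standardised differences, or f = 0.10 and f = 0.25 for an omnibus F test.
- Two-sided testing.
- No loss of scans. This favours the plan, since section 5.5 excludes scans for motion and artifact.

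The protocol has no numerical power figure to reproduce, so the check is whether N = 40 delivers the stated property.

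**Step 1. Effect in SDs of the within-person change (dz).** Power is that of a paired t-test: df = n − 1 and noncentrality = dz × √n. For n = 40 and dz = 0.2, noncentrality = 0.2 × √40 = 1.265, against a critical value of 2.023 on 39 df.

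| dz | Power, n = 40 |
|---|---|
| 0.2 | 23% |
| 0.3 | 46% |
| 0.45 | 79% |
| 0.5 | 87% |

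Power of 80% is reached at dz = 0.454. The normal approximation gives 24% power at 0.2 and (1.960 + 0.842)/√40 = 0.443 for 80% power. For dz = 0.2 at 80% power, 199 participants would be needed. One-sided testing raises power at 0.2 only to 34%. With 36 usable participants, two-sided power at 0.2 is 21%.

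**Step 2. Effect in between-person SDs (d).** Section 3.4 expresses circuit scores in SD units of a healthy reference sample, so this metric is also natural. With within-person correlation ρ, dz = d/√(2(1 − ρ)). For d = 0.2 and n = 40:

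| ρ | dz | Power |
|---|---|---|
| 0.2 | 0.158 | 16% |
| 0.5 | 0.200 | 23% |
| 0.8 | 0.316 | 50% |
| 0.9 | 0.447 | 79% |

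Setting dz = 0.454 gives ρ = 1 − ½(0.2/0.454)² ≈ 0.90 as the correlation needed for 80% power.

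**Step 3. Three-dose F test.** With f = 0.10, N = 40, m = 3 and λ = f²Nm/(1 − ρ), power is 25% at ρ = 0.5, 40% at 0.7 and 57% at 0.8. Power of 80% needs ρ of about 0.88.

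**Step 4. Interim look, N = 17.** The paired difference detectable with 80% power is dz = 0.72. Power for a medium effect depends on the metric:

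| Reading of medium | ρ = 0.5 | ρ = 0.7 | ρ = 0.8 |
|---|---|---|---|
| 0.5 between-person SD, paired contrast | 49% | 71% | 86% |
| f = 0.25, three-dose F test | 57% | 80% | 94% |

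On the within-person-change scale, dz = 0.5 gives 49% with no separate correlation involved.

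**Step 5. Median-split contrast (added information only).** Section 5.1 also says "We will focus on the between-subgroup difference between placebo and 120mg MDMA". With 20 against 20, df = 38 and noncentrality = d × √(20/2). Power of 80% needs a between-group difference of about 0.91 SD in the drug–placebo change.

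**The case against.** The strongest reply is that the protocol never defines *small*. The sentence may be only a qualitative statement of intent, with the inputs held in a statistical analysis plan not shown here. If the effect is measured in between-person SDs and circuit scores are very stable across sessions, N = 40 could reach 80% power. If *small* means a band running up to 0.5, then 0.45 falls inside it.

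Part of this stands. The 23% figure rests on one choice of metric and has to be reported with that choice. The absence of a calculation is not the finding. What does not stand is the defence by correlation: it needs about 0.88 to 0.90 between sessions, and the protocol neither states nor supports such a value. The band reading is not in the protocol either, and section 5.3 itself sets *small* apart from the *medium range*.

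Three stronger readings are tempting and should be resisted.

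- **That the N = 17 look is unsound.** A reader might infer that a medium effect would be found only about half the time. That is one case; at correlations of 0.7 to 0.8 power is 71% to 86% for the paired contrast. Section 5.3 says only that the effect *can be* medium and promises no power at the interim.
- **That the 0.91 SD subgroup figure contradicts section 5.3.** It does not. The power sentence concerns the effect of MDMA on brain activation, not a difference between baseline subgroups.
- **That the investigators will read a null as excluding a small effect.** The protocol does not say so, and section 5.3 has no futility or stopping rule. The risk of that reading is an inference from the power claim.

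**Conclusion.** The power property claimed in section 5.3 is not delivered by 40 participants under conventional readings of *small*. A standardised effect of 0.2 has 23% power on the within-person-change scale, and 16% to 79% on the between-person scale as the correlation goes from 0.2 to 0.9. The paired difference detectable with 80% power is 0.45 SD, close to a medium effect.

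This rests on small = 0.2 (f = 0.10 for the F test), two-sided 5% testing, a single test and 40 evaluable participants. The last two favour the plan. The conclusion would change only if a between-session correlation of roughly 0.88 to 0.90 or more were documented, or if *small* were explicitly defined as something near 0.45.

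The interim figures are conditional and do not show that the look at N = 17 is wrong. They do show that a non-significant interim result should not be taken as evidence against a medium effect unless a high correlation is established.

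**What to change.** Replace the power sentence in section 5.3 with one that names its metric, for example: *Forty evaluable participants give 80% power (two-sided 0.05, one test, no multiplicity correction) for a difference of 0.45 SD of the within-person drug–placebo change; power for 0.2 on that scale is 23%.* Alternatively, if a calculation supporting *small* exists, state its effect metric and within-person correlation.

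Then add:

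- a sentence saying that a null result does not exclude a small effect;
- the N = 17 sensitivity in conditional form: detectable paired difference 0.72; power for 0.5 of 49% on the within-person-change scale, or 49%, 71% and 86% at correlations of 0.5, 0.7 and 0.8 on the between-person SD scale; and a statement that a non-significant interim result is not evidence against a medium effect;
- separately, as information for readers of section 5.1, that the 20-versus-20 median-split contrast has 80% power only for a difference of about 0.91 SD in the drug–placebo change.

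The sample size should stay as it is. The cost is a few sentences and a less favourable stated sensitivity; no procedure or analysis changes.

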#### *2.6.4 Blinded personnel*

The study design is double blind, both the participant and the research team, including study clinicians, are blinded to the dose assignment. Blinded research staff includes clinical research coordinators, study clinicians, research nurses, and scanning personnel. All data collection is conducted by the blinded research team. Data analysts for both the interim analysis and the final analysis are unblinded.

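### Section 5.3 plans an unblinded detection look at 17 of 40 participants without saying what the look may claim or change; if either look counts at 0.05, per-test type I error is about 8.6%

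*Protocol*

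**What the plan says.** Protocol section 5.3 gives the planning basis as "We plan the power of our study to be able to detect a small effect of MDMA on brain activation". It then notes that published effects in similar tasks may be medium, and concludes: "we will run interim analyses to determine if our effects of interest can already be detected when we collect N = 17 participants".

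Other sections bear on this:

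- Section 2.10 sets the final size: "A total of 40 participants will be recruited".
- Section 2.6.4 shows that the interim and final analyses are separate: "Data analysts for both the interim analysis and the final analysis are unblinded".
- Section 5.1 models the primary outcomes "with Dose (placebo, 80mg MDMA and 120mg MDMA) as a within-subjects fixed effect". It names 120 mg versus placebo and 80 mg versus placebo as the comparisons of interest, including how they differ between baseline subgroups.
- Section 5.1 also says of the pre-registered primary measures: "we will not perform multiple comparison correction as they measure overlapping constructs and do not meet strict criteria for independent measures".
- The only significance threshold for drug effects is in section 5.1, as part of an alternative way of handling many measures: "identifying measures that show significant MDMA-induced effects using a $p < 0.05$ threshold".

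The protocol gives no level for the interim test and no stopping or continuation rule. It does not say what follows if an effect is detected at N = 17. The interim analysis that the monitoring board may recommend under section 6 concerns safety and is a different matter.

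**The concern.** Asking whether an effect can already be detected is, on its natural reading, an efficacy question, and the reason section 5.3 gives for asking it is also about efficacy. The look is made by unblinded analysts on the effects that will be tested again at the end. The reason given in section 5.1 for not correcting is that the measures overlap. That reason does not reach repeated testing of the same measure over time.

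As written, nothing prevents an effect from being declared at N = 17, or at N = 40 if the first look misses. Two things are then at stake. The false-positive rate of each test would exceed its nominal level. And an effect declared at N = 17 would tend to be exaggerated, because with so few participants only large estimates reach significance.

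**Working it through.** The protocol states no type I error or power figure for either analysis, so there is no figure of its own to reproduce.

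**Inputs**

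- Interim size 17 (section 5.3) and final size 40 (section 2.10), so the information fraction is 17/40 = 0.425 if all 40 are analysable.
- Two looks (section 2.6.4).
- A within-subject dose contrast (section 5.1), treated here as a paired contrast.
- Assumed: a two-sided 0.05 test at each look. Sidedness is not stated, and 0.05 appears only under the alternative approach in section 5.1.
- Assumed: a significant result at either look counts as a finding.

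**Type I error with two looks**

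Under the null hypothesis the two test statistics are approximately bivariate normal with correlation √(17/40) = 0.652. The error rate is P(|Z1| > 1.96 or |Z2| > 1.96) = 0.05 + 0.05 − P(both exceed 1.96). The joint probability is 0.0144, so the rate is 0.10 − 0.0144 = 0.0856, or 8.6%. A simulation of 1,000,000 pairs of paired t-tests at n = 17 and n = 40 gives 8.61%.

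| Analysable at the end | Correlation between looks | Type I error per test |
|---|---|---|
| 40 | 0.652 | 8.6% |
| 36 | 0.687 | 8.4% |
| 34 | 0.707 | 8.3% |
| 30 | 0.753 | 8.1% |

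If the N = 17 look supports no claim and only the final test counts, the rate is 5%.

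**Overestimation at N = 17**

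A paired t-test with 16 degrees of freedom needs |t| > 2.12. The observed standardised effect must therefore exceed 2.12/√17 = 0.51, whatever the true effect. The true effects below are assumed, because the protocol gives only the word small. The results come from 1,000,000 simulated looks for each value.

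| Assumed true paired effect | Significant in the right direction | Mean estimate when significant (sample SD) | Same, on the true-SD scale |
|---|---|---|---|
| 0.2 | 12% | 0.67 | 0.58 |
| 0.3 | 21% | 0.69 | 0.61 |
| 0.5 | 49% | 0.75 | 0.68 |

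The exaggeration is largest when the true effect is small. A non-significant look says little either: even at 0.5, about half of all looks miss.

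**Boundaries that hold 5% per test**

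With Lan-DeMets O'Brien-Fleming spending, the alpha used at the interim is 2 × [1 − Φ(1.96/√0.425)] = 2 × [1 − Φ(3.006)] = 0.0026. Solving for the final bound so that the overall error is 0.05 gives z = 1.969, that is p < 0.0489.

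**The case against.** The strongest reply is that the protocol does not set up the error rate computed here. It states no interim level, no stopping rule and no early claim. The 0.05 threshold belongs to an alternative screening approach and is not given as the level of the primary test. Interim boundaries are also commonly placed in a statistical analysis plan, which is not shown. All of this stands. The accurate statement is that no adjustment is described, not that one is ruled out, and the 8.6% is conditional.

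A reader might infer more than the text supports in three ways:

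- **That the trial will stop at 17.** This would leave the baseline median split with about 8 versus 9 participants. No section plans such a stop, and recruitment, the randomisation list for 40 study IDs and the separate final analysis all point to continuing.
- **That the interim look drives a very high chance of at least one false positive across circuit measures.** That figure depends on an assumed number of measures and an assumed correlation between them. With two dose contrasts, 8 measures and either look counted, it runs from 44% at correlation 0.8 to 72% at 0.2. Much of it comes from declining correction across measures, which is a separate matter.
- **That detection at N = 17 is already defined as success.** The wording leans that way but attaches no consequence to it.

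The reply does not remove the gap. The protocol itself commits to an unblinded look at a stated size for the purpose of detection, and does not limit what that look may claim or change.

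**Conclusion.** The point holds in conditional form. Section 5.3 fixes a detection-type look at N = 17 and leaves its status open. Type I error per test is about 8.6% if both looks use two-sided 0.05, either may be counted as a finding, and all 40 participants are analysable. It falls to 8.1% with 30 analysable, and it is 5% if only the final test counts. The excess is therefore at most 3.6 percentage points per test. Overestimation of any effect declared at N = 17 is the more visible practical risk, since every such estimate would exceed 0.51 on the sample scale.

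This should be fixed, but it does not invalidate the design. The study is mechanistic, continuation to 40 is the evident intention, and one paragraph settles it. The rule carries weight only if it is written before the look is taken.

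**What to change.** Replace the last sentence of section 5.3 with one of the following.

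1. **Descriptive look (simplest).** State that the analysis at N = 17 is descriptive, supports no efficacy claim, and does not stop or change the trial, and that hypotheses are tested only at the final analysis. Type I error stays at 5% per test. The cost is giving up an early claim.
2. **Formal boundary.** State a Lan-DeMets O'Brien-Fleming rule: p < 0.0026 at N = 17 and p < 0.0489 at N = 40. Apply it per test to every primary contrast examined at the interim: 120 mg versus placebo, 80 mg versus placebo, and the Dose-by-Subgroup contrasts. Any contrast without a boundary is left untested until the final analysis. The cost is a final threshold of 0.0489 instead of 0.05, with negligible loss of power.

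Under either option, add that interim results are not shared with the blinded data-collection team. Section 2.6.4 separates blinded collectors from unblinded analysts but does not expressly bar passing results between them. Neither option deals with multiplicity across circuit measures, which needs its own decision.

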### **5.4 Methods for additional analyses (e.g., subgroup analyses)**

A further novel aspect of our project will be to examine sex as a biological variable as a potential moderator of MDMA-induced effects on experience, behavior, and brain function. In healthy humans, biological sex has been implicated in the subjective and physiological impact of MDMA, although the data on these effects is very limited. The acute psychoactive effects of MDMA have been reported as more pronounced in women than in men. On the other hand, men report higher blood pressure effects on MDMA than women. To our knowledge, sex differences in the acute impact of MDMA on human neural circuit function have not been investigated.

